
**Fig. 1 Fig1:**
[figure not shown]
Study flow diagram

The social learning task, which will be used to measure changes in social cognition, is the only task, which will be administered before and after brain stimulation.

### Outcome measures

(a) In the facial recognition paradigm, the facial affect recognition ability of participants will be assessed using 28 digitally reworked photographs of faces. The photographs show the six basic emotions (happiness, fear, anger, surprise, disgust, sadness and neutral) and have been selected from Ekman and Friesen’s “Pictures of Facial Affect” [47]. Participants will have to choose the emotion that fits best to the shown photograph. For the subsequent analysis, the number of correct responses will be counted. We hypothesize that ASD individuals receiving verum-iTBS will demonstrate better results of facial affect recognition ability compared to ASD individuals receiving sham-iTBS.

(b) The social probabilistic learning task will be administered before and after iTBS [40]. In this task, participants have to integrate social and non-social information to learn which one of two cards leads to a reward. The winning probability of each card will change several times during the experiment, as will the helpfulness of the social cue. The participants will not be explicitly told to use social information. When selecting the winning card on a given trial, the number of points depicted on the card can be won. For the analysis, the main behavioural outcomes are the number of correct responses, the total score accumulated and the number of trials where participants considered social information. In addition, a hierarchical Gaussian filter model will be used to mathematically model how beliefs about the helpfulness of the social cues are learned and integrated with non-social beliefs about the probability of reward for each stimulus. Previous studies using dynamic learning tasks in conjunction with computational modeling have shown that high in autistic trait individuals find it difficult to integrate social and non-social cues and to form predictions about volatile environments [49, 50]. We hypothesize that ASD individuals receiving verum-iTBS compared to control treatment will demonstrate an increase in the number of correct responses and in the proportion of trial where they follow social cues. With computational modelling, we aim to examine the underlying cognitive mechanisms that bring about these behavioral outcomes. We hypothesize that iTBS will improve the ability to integrate social and non-social information, as measured by a social weighting parameter, while not having an effect on how participants update beliefs in the non-social domain.

(c) The 3-back task will be used as a control task to measure a domain of the executive functions by testing participants’ working memory and memory capacity [46]. Participants will be presented with a series of alternating stimuli (numbers) changing in random sequence, eventually repeating and will be asked to report when a stimulus matches another stimulus presented three trials back (*N* = 3). The number of correct responses and reaction time will be counted. No improvement in participants´ executive function ability after neuronavigated iTBS is anticipated.

(d) The coin rotation task, also a control task, will be used to access participants´ fine motor skills [48]. Participants will be asked to take a coin between their thumb, forefinger and middle finger and spin it between these fingers as quickly as possible without dropping it for 15 s. Three attempts will be allowed but only the second and third will be counted. The number of 180^o^ coin rotations in 10 s will be counted. The performance will be recorded with a camera and further analyzed offline using slow motion. We hypothesize that ASD participants will not demonstrate improvement in their motor skills after iTBS.

Table 1 offers an overview of the key instruments that will be used in the study.

**Table 1 Tab1:** Overview of instruments

Instruments	Measured construct
Autism Spectrum Quotient	Autistic traits
Intelligence Quotient/MWT	Mental ability
Beck Depression Inventory	Depressive symptomatology
Social localizer	Brain connectivity
N-back task	Working memory
Facial recognition paradigm	Affect recognition
Social task	Probabilistic learning
Coin rotation task	Motor skills

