### Sample size calculation

A power analysis with an estimated effect size of 0.3, a power of 0.8 and an alpha error of 0.05 was used to determine the required sample size for this study using G* Power [41]. Based on this analysis 90 participants are required. In order to divide the participants in four groups a total sample of 92 participants is required. Taking possible drop-outs as well as loss of data due to technical problems into account we have decided to include 52 participants in each arm of the study, i.e. 52 participants with ASD and 52 participants without ASD. Only little prior evidence exists in the field of neuronavigated TMS in adults with ASD, so that no prior studies could serve as a basis for the power analysis. Since this is a proof-of-concept study we opted for a small effect size, so that even smaller effects of the intervention can be detected.

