An important strength of this study will be its relatively large sample size. As already mentioned, the few existing TMS studies in adults with autism have had relatively small sample sizes [29]. Our target of 104 participants will ensure statistical power to test our hypothesis. Another strength of the current study is the use of neuronavigation to localize the personalized target, which ensures accurate and consistent targeting of the region of interest, thus minimalizing variability and increasing validity of our findings. Furthermore, the utilization of iTBS is a strength, as it offers a more time-efficient and potentially more effective stimulation paradigm [38]. A limitation of this study could be employing only a single session of TMS, as multiple sessions could yield cumulative effects and better measurable results. Another limitation could be the single-blind study design. However, the primary endpoint tasks are highly standardized and the entire evaluation process is computerized, thereby minimizing any effects arising from the lack of blinding.

If this study succeeds in demonstrating that personalized TMS can modulate social cognition in adults with ASD without intellectual impairment, this may serve as an important stepping stone towards studies with larger sample sizes, more TMS sessions and maybe different TMS protocols.

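### No single variable decides the lead hypothesis, and the sample size, which fits one test at 0.05, is tied to no outcome

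*Protocol article*

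**What the plan says.** - **Objectives.** The lead hypothesis is an iTBS-induced improvement in social information processing in adults with ASD, measured by the probabilistic learning task. No variable of the task is named. Executive function, brain activation and connectivity are listed as secondary; facial recognition is not.
- **Outcome measures (b).** For the learning task, "the main behavioural outcomes are the number of correct responses, the total score accumulated and the number of trials where participants considered social information". Improvement under verum stimulation is predicted for correct responses and for the proportion of trials on which the social cue is followed. No direction is predicted for the total score. Integration of social and non-social information is also predicted to improve, "as measured by a social weighting parameter".
- **Outcome measures (a).** Better facial affect recognition is predicted for ASD verum than for ASD sham.
- **Analysis plan.** The 3-back, facial recognition and coin rotation tasks get two-way ANOVAs. For the learning task, only the model parameters are described in detail, in mixed ANOVAs. No outcome is ranked above another.
- **Sample size calculation.** "A power analysis with an estimated effect size of 0.3, a power of 0.8 and an alpha error of 0.05 was used". The result is "Based on this analysis 90 participants are required. In order to divide the participants in four groups a total sample of 92 participants is required". The target is then set at "52 participants with ASD and 52 participants without ASD". No outcome, effect or contrast is named.
- **Discussion.** "the primary endpoint tasks are highly standardized", with tasks in the plural. The same section says that 104 participants secure power for the hypothesis, in the singular.

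**The concern.** The article speaks of one hypothesis and one power calculation, but uses the labels main and primary for several measures. A reader cannot tell whether the trial is decided by a behavioural count, by the total score or by the model parameter, or whether facial recognition also counts.

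Two things are at stake. First, the headline variable can be chosen after the results are seen, which raises the chance of a false claim of benefit. Second, the statement in the Discussion about power cannot be checked, because power belongs to a particular variable and contrast. Several of the hypotheses compare verum with sham within ASD, which uses only half of the sample.

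**Working it through.** **1. Count the hypothesised outcomes.**

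| Measure | Called main | Improvement hypothesis |
|---|---|---|
| Correct responses | yes | yes |
| Total score | yes | no |
| Trials using social information | yes | yes |
| Social weighting parameter | no | yes |
| Facial affect recognition | no | yes |

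Four outcomes carry an improvement hypothesis. The three labelled main are not the same set.

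**2. Reproduce the plan's sample size.** The inputs are "an estimated effect size of 0.3", and "a power of 0.8 and an alpha error of 0.05". The metric of the effect size is not named; Cohen's f is assumed. For a 1-df effect in a four-group ANOVA, the non-centrality is λ = f²N with N − 4 error degrees of freedom.

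- N = 90: λ = 0.09 × 90 = 8.10, power 0.804. This is the smallest N that reaches 0.80, so the stated 90 is reproduced.
- N = 92: λ = 8.28, power 0.812.
- N = 104: λ = 9.36, power 0.858.

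Some other readings do not give 90: a 3-df test needs 126, and a two-group comparison with d = 0.3 needs 175 per group. A paired test with a standardised difference of 0.3 also gives 90. On either reading that fits, the calculation is for one unadjusted test.

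**3. Family-wise error.** Assume that the four outcomes are each tested two-sided at 0.05, that none is affected, and that any one significant result counts. If they are independent:

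- any significant result: 1 − 0.95⁴ = 0.185
- a significant result in the improvement direction: 1 − 0.975⁴ = 0.096

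The documents give no correlations. Simulation with equally correlated normal test statistics gives:

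| Assumed correlation | Any direction | Improvement only |
|---|---|---|
| 0 | 18.5% | 9.6% |
| 0.7 | 13.0% | 6.5% |
| 0.9 | 9.4% | 4.7% |
| One test, for reference | 5% | 2.5% |

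**4. What sharing alpha would cost.** With Bonferroni over four outcomes, alpha is 0.05 / 4 = 0.0125. The same power function then needs N = 128. Power per test is 0.629 at 92 and 0.696 at 104.

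**5. Power for the contrast within ASD.** Assume equal cells: 92 / 4 = 23 and 104 / 4 = 26. An f of 0.3 for two equal groups corresponds to d = 2 × 0.3 = 0.6. An unadjusted two-sided t test of ASD verum against ASD sham then has power 0.51 with 23 per cell and 0.56 with 26. Baseline adjustment would raise this by an amount that depends on the pre-post correlation, which is not given.

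**The case against.** **The false-positive argument rests on inferred rules.** A reader might infer that every outcome is tested at 0.05 and that any one success would support the claim. The article says neither. It gives 0.05 only for planning. A test order or adjustment may stand in an analysis plan that is not shown, so its absence here is no finding. The two behavioural predictions are joined by a conjunction; if both had to succeed, error would not be inflated. All of this stands, and it makes the family-wise figures conditional.

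**A reader might also count five superiority hypotheses.** The text supports four, because the total score has none.

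**The inflation is smaller than the independent figures suggest.** Three of the four outcomes come from one task and are probably correlated. A false claim of improvement needs a result in the right direction, which leaves 9.6% to 4.7%. This stands too, but the like-for-like reference is 2.5%, so some inflation remains over the whole range shown.

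**There is an implicit order.** The lead hypothesis names one task, the only one given before and after stimulation. The modelling is introduced as an addition that explains the behavioural results, and the study is described as proof of concept. This narrows the field to the learning task. It does not choose among that task's variables, and the Discussion's plural undoes part of the narrowing.

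What remains is not an effect of condensing. The article itself discusses main outcomes, primary endpoints and power, and its statements do not settle on one variable.

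**Conclusion.** The point holds in a limited form: the primary variable is not fixed, and the power calculation is not attached to one. It does not show that an uncorrected multiple-testing procedure is planned.

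If four outcomes were tested at the planning alpha and any success counted, family-wise error would be about two to four times the planned 5% (9.4% to 18.5%). In the improvement direction it would be 4.7% to 9.6%, against 2.5%. The correlations of 0 to 0.9 are assumptions.

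With one primary 1-df test that uses all four groups, the planned size is adequate for f = 0.3 (power 0.858 at 104, before any drop-out). That does not carry over to a contrast within ASD, where d = 0.6 gives 0.51 to 0.56 without baseline adjustment. The choice of variable and contrast therefore determines whether the Discussion's statement on power is true. It should be settled, and the change is one of wording.

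**What to change.** Before any outcome is compared by stimulation condition:

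1. Name one learning-task variable and one contrast as primary. ASD verum against ASD sham after stimulation, adjusted for the pre-stimulation value, matches the lead hypothesis. The social weighting parameter is a reasonable candidate, because the Objectives stress integration of social information. A behavioural measure would also fit, and the choice is the investigators'.
2. State which test the sample size calculation refers to. If it is not the primary contrast, restate the power for that contrast, with the effect-size metric and the assumed pre-post correlation.
3. Test the other hypothesised outcomes as secondary, in a fixed order or with Holm's procedure, and say what role the total score has.
4. Make the Discussion's reference to primary endpoint tasks agree with this.

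The cost is wording in the protocol, the analysis plan and the registry entry, and some loss of power for the secondary outcomes. No added assessments are needed. If the restated power turns out too low, that is a limit of the present design that should be stated openly.

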### Objectives

To optimally probe the effects of rTMS in the rTPJ in ASD, we will combine the afore mentioned state-of-the-art stimulation techniques, including individualized fMRI-guided targets, time-efficient intermittent theta-burst-stimulation (iTBS) and a stereotactic neuronavigation.

In our study on the basis of the current literature the neurocognitive pathway of mentalizing will be localized using a well-established video-based fMRI task, which contrasts brain activation during scenes with socially engaging vis-a-vis socially neutral content [39]. This has been shown to consistently localize activation maxima in regions involved in social cognition including the dmPFC and TPJ on the single-subject level [39]. In a second session, each participant’s activation maximum in the rTPJ will be used as a stimulation target to conduct a neuronavigated iTBS intervention with the aim of modulating social information processing. The effects of the stimulation will be measured by using a test battery encompassing social cognitive as well as cognitive control tasks.

We hypothesize that adults with ASD without intellectual impairment will show an iTBS-induced improvement in social information processing, measured by an established probabilistic learning task that requires the integration of both social and non-social information [40]. In particular, participants with ASD without intellectual impairment belonging to the treatment group will show an increased ability to integrate social information into their decision-making process compared to the control group. We hypothesize that these effects are not due to changes or baseline differences in executive functioning.

Secondary analyses will investigate group differences in executive function tests as well as brain activation and connectivity in the ASD and control group.

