### Analysis plan

#### Demographic data and behavioral tasks analysis

All behavioral data will be analyzed using the statistical software IBM SPSS Statistics. For the analysis a two-way factorial ANOVA will be used. More precisely for the 3-back task response accuracy will be recorded and two-way ANOVAs will be used for comparisons between groups. For the facial recognition paradigm, the number of correct responses will be recorded and two-way factorial ANOVAs will be used for between groups comparisons. For the coin rotation task, the number of 180° coin rotations in 10 s will be recorded and two-way factorial ANOVAs will be used for comparisons between groups.

The probabilistic learning task will be analyzed using the Hierarchical Gaussian Filter (HGF) model to infer participants’ individual belief trajectories concerning the cards and the social cues. Model comparisons will be carried out by means of Bayesian Model Selection. Group-specific differences in model parameters will be evaluated by means of mixed ANOVAs with schedule stability as a within-subject factor, information type as the within participant factor (social vs. card). Groups and brain stimulation will be the between subject factors.

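### The 3-back, the only executive-function measure, is given a raw score that mixes working memory with willingness to respond; this mainly exposes the ASD–control comparison

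*Protocol article*

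**What the plan says.** All references are to the Protocol article.

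- **Task.** Outcome measures (c) describes a response for matches only: participants "will be asked to report when a stimulus matches another stimulus presented three trials back". It gives no response rule for non-matches.
- **Score, Outcome measures (c).** "The number of correct responses and reaction time will be counted".
- **Score, Analysis plan (Demographic data and behavioral tasks analysis).** "More precisely for the 3-back task response accuracy will be recorded and two-way ANOVAs will be used for comparisons between groups". Reaction time is not taken up there.
- **Role.** "The 3-back task will be used as a control task to measure a domain of the executive functions". It is the only task described as measuring executive function; the other control task, coin rotation, measures motor skill.
- **Inference it supports.** Objectives, on the expected social effects: "We hypothesize that these effects are not due to changes or baseline differences in executive functioning". Group differences in executive-function tests are also listed there as a secondary analysis.
- **Timing.** Under Fig. 1, the social learning task "is the only task, which will be administered before and after brain stimulation", so the 3-back has no pre-stimulation value.

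Neither section mentions false alarms or a sensitivity index.

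**The concern.** When people signal matches, two things determine the raw score: how well they tell matches from non-matches, and how much evidence they want before responding. If correct responses are hits, responding on every trial earns the maximum. If correct omissions also count, never responding earns the non-target share. Two groups with equal working memory but different response caution can therefore differ on the score, and groups with different memory can look alike.

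At stake is the executive-function comparison, and through it the argument that a social effect is specific. With no baseline 3-back, a person's habitual response style cannot be subtracted out.

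**Working it through.** **1. The plan's own figure.** The article gives no figure for the 3-back. Its only calculation is the sample size: "A power analysis with an estimated effect size of 0.3, a power of 0.8 and an alpha error of 0.05", leading to 90 participants. Reading 0.3 as Cohen's f with one numerator degree of freedom, the noncentral F distribution gives N = 90 (power 0.803), so the figure reproduces. It is used here only for group sizes. The planned 104 participants give 104/2 = 52 per diagnostic group and, if allocation is 1:1 (ratio not stated), 104/4 = 26 per cell.

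**2. Model and assumed inputs.** Equal-variance signal detection, with sensitivity d', criterion c (0 neutral, positive cautious), target share p and standard normal distribution function Φ:

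- hit rate H = Φ(d'/2 − c)
- false-alarm rate FA = Φ(−d'/2 − c)
- accuracy = p·H + (1 − p)(1 − FA)

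The article gives none of d', c, p or the number of trials. All are assumed below, with p from 20% to 50%.

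**3. Same memory, different caution (d' = 1.5).** Example at c = 0.6, p = 25%: H = Φ(0.15) = 0.560; FA = Φ(−1.35) = 0.089; accuracy = 0.140 + 0.684 = 0.824.

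| c | H | FA | Accuracy, p = 20% | 25% | 33% | 50% |
|---|---|---|---|---|---|---|
| 0 | 0.773 | 0.227 | 0.773 | 0.773 | 0.773 | 0.773 |
| 0.3 | 0.674 | 0.147 | 0.817 | 0.808 | 0.794 | 0.763 |
| 0.6 | 0.560 | 0.089 | 0.841 | 0.824 | 0.795 | 0.736 |

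Moving c from 0 to 0.6 lowers hits by 0.773 − 0.560 = 21.3 points. Accuracy changes by between +6.8 points (0.841 − 0.773, at 20% targets) and −3.7 points (0.736 − 0.773, at 50%). Both scores move with memory fixed, hits much more.

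**4. Different memory, same hits.** The pairs d' = 2.0 with c = 0.6, d' = 1.5 with c = 0.35, and d' = 1.0 with c = 0.10 all give H = Φ(0.40) = 0.655. Their false-alarm rates are 0.055, 0.136 and 0.274. At 25% targets, accuracy does separate them (0.873, 0.812, 0.708).

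**5. Consequence at this sample size.** Two-sample t-tests at the 5% level, 4,000 simulated trials, 100 task trials, 25% targets, between-person SD 0.6 for d' and 0.3 for c. Entries are percentages of simulated trials with a significant difference.

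| Scenario | n per group | Hits | Accuracy | d' |
|---|---|---|---|---|
| Equal d' 1.5; c 0.3 vs 0.6 | 26 | 56.6 | 11.6 | 5.4 |
| | 52 | 85.6 | 17.7 | 4.8 |
| Equal d' 1.5; c 0 vs 0.3 | 26 | 55.4 | 23.5 | 4.9 |
| | 52 | 83.6 | 43.0 | 4.6 |
| d' 2.0 vs 1.5; c 0.55 vs 0.30 | 26 | 5.4 | 85.4 | 71.0 |
| | 52 | 4.9 | 98.8 | 94.5 |
| d' 2.0 vs 1.5; c 0 vs 0.45 | 26 | 99.7 | 12.4 | 70.9 |
| | 52 | 100.0 | 21.7 | 95.6 |

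With equal d' and equal c, all three scores reject in about 5%. The first two scenarios show a spurious difference. The third shows a real difference hidden in hits, and the fourth one largely hidden in accuracy. The last two were chosen to show masking. The data were generated from the model that defines d', which favours d'.

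**The case against.** **Hits-only scoring is not stated.** On an ordinary reading, the number of correct responses and response accuracy are one quantity, as a count and as a proportion. This stands. A reader might infer that the two sections rank the same people in opposite order. With d' = 2, 25% targets and c = −0.75 versus +0.75, hits are 96% versus 60% (a 36-point gap) while accuracy is 69% versus 87% (18 points the other way). That needs one section to mean hits and the other overall accuracy, which the text does not say. It also sets two hypothetical people 1.5 criterion units apart, not two plausible group means.

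**The magnitude is assumed.** This stands. Nothing in the article shows a criterion difference between any groups. On the accuracy reading, the spurious rejection rates are 12% to 43%, not 55% to 86%.

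**The stimulation contrast is randomised.** This also stands. A reader might infer that verum versus sham on the 3-back is biased. Block randomisation balances habitual response style in expectation, so that contrast is affected only by chance imbalance or if iTBS itself shifts criterion. The article suggests no such shift.

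**Scoring detail belongs in a fuller document, and percent correct is a legitimate score.** This stands only in part. Trial counts and response keys can be left out of an article. But this article names the score in two places and names the test applied to it, and both raw scores depend on criterion whatever those details are. Reaction time does not separate sensitivity from caution, and the Analysis plan does not analyse it.

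**Conclusion.** The point holds as a low-cost improvement to a supporting measure. Whichever raw score is meant, it depends on response criterion as well as on working memory. The distortion is large if the score is hits (55% to 86% spurious rejection for an assumed criterion difference of 0.3) and smaller if it is overall accuracy (12% to 43%), against about 5% for d'. These figures rest on the assumed d', criterion, target share, trial count and between-person spread, and on the equal-variance model.

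The ASD versus control comparison of executive function is directly exposed, because diagnosis is not randomised and there is no baseline 3-back. Verum versus sham is exposed only through a stimulation effect on criterion or chance imbalance. It would go too far to say that the main social outcome is compromised: it comes from a different task and does not use this score. What is weakened is the supporting argument that social effects are not executive in origin.

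**What to change.** In Outcome measures (c) and in the Analysis plan, name the same single 3-back outcome for the two-way ANOVA: a sensitivity index built from hits and false alarms. Choose one in advance. One option is d' with the log-linear correction (add 0.5 to the hit and false-alarm counts and 1 to the numbers of targets and non-targets). The other is hit rate minus false-alarm rate. Report criterion, raw accuracy and reaction time on hits descriptively.

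The cost is a small change to the scoring script, provided false alarms are logged; confirm this before further data are collected. No extra participants or task time are needed. The new score is slightly less directly comparable with studies that report raw accuracy, which the descriptive reporting largely covers.
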